## Abstract

**Background:**

Gadget addiction is a common behavioral problem among children. It is known to hamper social and academic life as well as adversely affect the lives of children. Ayurveda offers many therapeutic modalities and Ayurvedic medicines that can be used in the management of gadget addiction in children. The purpose of this study is to evaluate and compare the effectiveness of nonpharmacological therapies and the pharmaceutical intervention Medhya Rasayana in treating childhood gadget addiction.

**Objective:**

This study aims to provide a detailed description of the study methodology that will be used to compare the efficacy of nonpharmacological versus pharmaceutical interventions in the treatment of children’s gadget addiction.

**Methods:**

A randomized, parallel, triple-arm interventional study will be conducted on diagnosed participants of gadget addiction with an age group of 6- to 16-year-old children, which will be selected and equally distributed in 2 groups. Group P will be given Medhya Rasayana (pharmacological intervention), group N will be nonpharmacological Ayurveda intervention, and group C (cognitive behavioral therapy) will be an external group. The Study duration is 180 days with assessment at baseline, midpoint, and endpoint Appropriate statistical techniques, such as ANOVA and regression analysis, will be used to examine the data and evaluate the efficacy of the 3 groups’ interventions. We will perform subgroup analysis according to initial addiction severity, gender, and age. Primary outcome measures include a reduction in gadget addiction and changes in the psychosocial well-being of participants. Standardized questionnaires and instruments will be used to collect data.

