##### Alternative Hypothesis (H1)

At least 1 intervention among the Medhya Rasayana and Ayurveda nonpharmacological intervention are more effective than the control group in reducing gadget addiction in children.

The purpose of this hypothesis is to determine whether the 3 interventions under comparison in the study differ in their efficacy. If statistically significant differences exist in the outcomes, researchers can ascertain them by testing the null hypothesis against the data gathered during the randomized controlled trial.

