## Methods

### Study Design

A 3-arm superiority randomized controlled trial will be performed. The study flow is depicted in Figure 1. Patients with gadget addiction will be selected from the Kaumarbhritya Outpatient Department of MGACHRC Salod, Wardha as per inclusion criteria mentioned in Textbox 2. During the first visit, Parents will be asked whether they would like to deaddict their child from gadget addiction if they are willing then written informed assent will be obtained from the participants’ guardian. Participants will then complete questionnaires on the internet addiction test scale and digital addiction scale. Furthermore, participants’ social behavior and Prakruti (physical and mental constitution) will be assessed. As well as age, gender, socioeconomic status, and type of gadget he or she is using frequently, and the purpose of gadget use will be assessed. After this period, participants will be randomly allocated to both intervention groups in a 1:1 allocation ratio. After this, Medhya Rasayana will be prescribed to participants in group I according to age-wise doses at a frequency of twice a day for a period of 90 days as mentioned in Table 1. Participants allocated to group II will be counseled regarding the adverse effects of gadget addiction on physical and mental health and advised to follow the following routine daily for a period of 90 days, details of nonpharmacological interventions are described in Tables 1 and 2. Yoga (sun salutations, meditation), Targeted reduction in Gadget use time Padanshik krama, that is, reduce gadget use time by one-fourth part each week. Reduced time will be used for adventure, bravery, cognitive skill-oriented things, sports, and yoga. Patients will be counseled to play indoor and outdoor games daily. Encouragement toward attending social programs whenever required and feasible, encouragement of parent-child relationship by advising parents to spend a minimum of 2 hours of quality time daily with children and to give a reward for not using mobile with encouraging children to learn new things, participate in group activities with peers and teach etiquette. Initial training in sun salutation and the method of meditation will be given to participants and their parents at the time of enrollment. Children will be asked to do the proposed sun salutation and meditation on the assessment day. Participants not responding or not following instructions will be eliminated from the study. Group III will be the external group due to the fact that cognitive behavioral therapy requires trained professionals and there are time and financial constraints as well. Hence, in this published data of previously conducted clinical trials, cognitive behavioral therapy intervention in the management of gadgets or internet addiction will be used for comparison with Medhya Rasayana and Ayurveda nonpharmacological interventions. On the 30th, 60th, and 90th days of treatment, participants will be evaluated using the internet addiction test scale and the *DSM-5* (*Diagnostic and Statistical Manual of Mental Disorders, Fifth Edition*) scale for social behavior. A follow-up will be conducted on the 180th day to determine whether the intervention’s possible effects are lasting.

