#### Statistical Analysis

The data collection phase will be concluded with statistical analysis. Repeated measures ANOVA test, and chi-square test, will be used for statistical interpretation. A statistician consultation will be considered for the selection of the proper statistical method.

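### ANOVA and regression are assigned to all three groups, but group C is published data from other trials; including it either needs child-level data that are not indicated or leaves between-trial variance out of the P-C and N-C standard errors

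*Protocol article*

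**What the plan says.** The abstract's Methods paragraph states that "Appropriate statistical techniques, such as ANOVA and regression analysis, will be used to examine the data and evaluate the efficacy of the 3" groups' interventions, and adds subgroup analyses by baseline severity, gender and age. The Statistical Analysis section states: "Repeated measures ANOVA test, and chi-square test, will be used for statistical interpretation". It continues: "A statistician consultation will be considered for the selection of the proper statistical method".

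On the make-up of the groups, the abstract says that "group C (cognitive behavioral therapy) will be an external group". Study Design says "participants will be randomly allocated to both intervention groups in a 1:1 allocation ratio", meaning P and N, and that "published data of previously conducted clinical trials, cognitive behavioral therapy intervention in the management of gadgets or internet addiction will be used for comparison". Table 1 gives 80 participants each to P and N. For C it gives no number, and its duration, assessment days and follow-up are dashes.

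The comparison with C is central to the plan. The third primary objective compares all three modalities, and the alternative hypothesis is that at least one Ayurveda intervention is among those that "are more effective than the control group in reducing gadget addiction in children". CBT is the only comparator outside the two Ayurveda groups.

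**The concern.** The named methods are designed for children observed within one study. Group C consists of results from other studies, run elsewhere and on their own schedules. There are two consequences.

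1. Methods that need each child's scores or covariates have nothing to work on for C unless the original investigators supply individual data.
2. Where a test can be assembled from published figures, its error term reflects only variation between children. It contains nothing for the difference between one trial's mean change and another's.

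At stake are the P-C and N-C contrasts, on which H1 and part of a primary objective rest. Their intervals would be too short, and the 5% type I error rate in the sample size section would not apply to them. The point concerns the standard error and which models can be fitted. Bias from the lack of randomisation is a separate problem that adds to this one.

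**Working it through.** **The plan's own figure.** The Participants section uses z values 1.64 and 0.84, P1 = 0.622, P2 = 0.362 and a difference of 0.20. Summing the two variance terms before multiplying gives:

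N = (1.64 + 0.84)² × [0.622 × 0.378 + 0.362 × 0.638] / 0.20² = 6.1504 × 0.466072 / 0.04 = 71.7, so 72 per group; 72 / 0.90 = 80.

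Both stated figures reproduce. The calculation gives no size for C and no allowance for variation between trials. The z of 1.64 is a one-sided 5% value.

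**Which methods can include C**

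| Method named | Needed for C | Available from published summaries? |
|---|---|---|
| Repeated measures ANOVA | Scores by child and visit, or the within-child covariance | Not normally; SD of change / SD is 1.265, 1.000 or 0.632 for a within-child correlation of 0.2, 0.5 or 0.8 |
| Regression with child-level covariates; subgroups | Covariates and outcome for each child | No |
| One-way ANOVA | Size, mean and SD | Yes, if reported |

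The last row was checked on a simulated three-group data set: F = 0.9615 from the raw data and the same from size, mean and SD alone.

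**What the one-way route leaves out.** The documents give no SD of change, no size for C and no between-trial SD (τ). The assumptions are:

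- SD of change in the internet addiction test (IAT) score: 12 or 15 points
- n_P = 80, from Table 1
- One CBT source trial with n_C = 40, 80 or 200
- τ = 2, 3 or 5 points

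This trial and the CBT trial each carry τ², so the difference between them carries 2τ².

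- SE used by ANOVA = SD × √(1/80 + 1/n_C)
- Actual SE = √(SE_ANOVA² + 2τ²)
- Actual two-sided error = 2 × [1 − Φ(1.96 × SE_ANOVA / actual SE)]

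Worked case, SD 12, n_C 80, τ 3: SE_ANOVA = 12 × √(2/80) = 1.897. Actual SE = √(3.60 + 18) = 4.648, a ratio of 2.45. Error = 2 × [1 − Φ(0.80)] = 0.42.

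| τ (points) | Lowest (SD 15, n_C 40) | Highest (SD 12, n_C 200) |
|---|---|---|
| 0 | 5% | 5% |
| 2 | 16% | 34% |
| 3 | 27% | 49% |
| 5 | 46% | 67% |

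With 1.645 in place of 1.96 and one tail, to match the plan's one-sided z, the ranges are 12-21%, 18-28% and 27-36%.

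**With several CBT trials.** The added variance becomes τ²(1 + 1/k) for k source trials. In SD units, with n_P = 72, n_C = 80, k = 3 and τ = 0.2 SD, the SE rises from 0.162 to 0.282 and the two-sided error is 25.9%. More source trials reduce the problem but do not remove it, because this trial's own τ² stays.

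**The chi-square test** on published counts has the same gap. With a proportion of 0.362 and an assumed 72 per group, the SE is √(2 × 0.362 × 0.638 / 72) = 0.0801. A between-trial SD of 0.05 raises it to √(0.0801² + 2 × 0.05²) = 0.1068, and the error to 14.2%. A between-trial SD of 0.10 gives 0.1625 and 33.4%.

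**The case against.** The strongest reply is that no single sentence plans a three-group repeated measures model. The three-group sentence is in the abstract and says only ANOVA and regression, as examples. Repeated measures ANOVA is named in a section that does not mention C. The dashes for C in Table 1 are footnoted as not applicable, which may mean that C lies outside the visit schedule and the model. Using published CBT results for comparison is compatible with a separate external comparison, and a statistical analysis plan not shown here could set one out.

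Part of this stands. A reader might infer that the three-group analysis cannot be computed at all. The documents do not support that, since a one-way ANOVA can be formed from published summaries. That only summaries will be available is itself an inference from the reference to published data, although nothing in the article points to individual records. A reader might also suppose that the CBT trials will be picked after P and N results are known; the article does not say when they are chosen. Nor do the error rates above describe this trial: they depend on an assumed τ, and with τ = 0 there is no inflation.

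What does not stand is that this is merely omitted detail. The abstract assigns the methods to all three groups, H1 and a primary objective depend on the comparison with C, and the possible statistician consultation commits the trial to nothing.

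**Conclusion.** The point holds in limited form. Repeated measures ANOVA, child-level regression and the subgroup analyses cannot include C without individual data. A one-way ANOVA can, but it treats other trials' patients as a concurrent sample and understates the P-C and N-C standard errors whenever τ is above zero. The direction does not depend on the figures assumed. The size does: with one CBT source and the stated ranges for SD and n_C, a nominal two-sided 5% test has a true error of about 16-34% at τ = 2, 27-49% at τ = 3 and 46-67% at τ = 5 points.

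It would be wrong to extend this to the whole trial. P versus N is randomised and sound on this point if analysed alone, and the sample size of 80 per group is not affected.

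**What to change.** 1. State that ANOVA, regression and the subgroup analyses cover the randomised P versus N comparison only.
2. For CBT, write the criteria for choosing source trials before any P or N outcome is analysed: age range, use of the IAT, baseline IAT range and an assessment near day 90.
3. Pool the mean change of those trials by random effects. Compare each arm with the pooled value using SE = √(SE_arm² + SE_pooled² + τ²). SE_pooled already carries the source trials' share of τ²; the last term is this trial's own.
4. If there are too few source trials to estimate τ (with one it cannot be estimated), show the result over a stated range of τ.
5. Label the result as a non-randomised external comparison. Reword H1 and the third primary objective so that superiority over CBT is not claimed as a randomised finding.

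This needs a literature extraction and changes to the hypothesis, objective and analysis wording, but no extra participants. The price is wider intervals and a weaker conclusion about CBT. Bias from the external group remains, since a wider interval does not remove it.

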**Results:**

In December 2023, the randomized controlled study got underway. Since participants may begin at any time, our goal is for everyone to be finished by December 2024.

**Conclusions:**

This research will provide crucial new information about the relative effectiveness of Ayurveda nonpharmacological therapies and Medhya Rasayana in treating children’s gadget addiction. The results will guide evidence-based treatments aimed at reducing the negative impact of excessive gadget use on this susceptible population’s psychosocial development. In the end, the findings are meant to help policy makers and medical professionals create sensible plans to deal with the rising issue of childhood gadget addiction.

**International Registered Report Identifier (IRRID):**

PRR1-10.2196/51833

## Introduction

### Overview

In the modern era, technology has affected life in various ways. One of the evolutions in the world of technology is electronic gadgets, which are used for entertainment, communication, information, education, and business. Moderate use of electronic gadgets improves the quality of life, but they also have the potential to be misused and cause gadget addiction. In general, addiction terminology was only associated with addiction to drugs, alcohol, and tobacco, but in the recent era, addiction may be defined as a process whereby a behavior that can function both to produce pleasure and to provide relief from internal discomfort is used in a pattern characterized by recurrent failure to control the behavior and continuation of the behavior despite significant negative consequences (unmanageability) [1]. Gadget addiction is a broad term that includes excessive use of mobile devices, internet games, internet-based gambling, excessive surfing on the internet, and excessive use of social media [2]. Gadget addiction is adversely associated with psychosocial disorders among children in the adolescent age group [3], as well as musculoskeletal problems and visual disturbance [4]. Gadget addiction leads to a reduction in physical activities, which results in fat deposition at an early age [5]. Research reveals that stressful environmental conditions promote human addiction [6]. Gadget addiction is a type of behavioral addiction; these addictions are similar to drug addiction except that in the case of gadget addiction, the person is not addicted to the substance but to the behavior or feeling brought about by the use of a gadget [7]. The mesolimbic brain circuit plays a significant role in behavior due to addiction [8]. All addictive substances increase the feeling of joy and this trend leads to their repeated use.

Previous studies by Ayurveda scholars reveal only the prevalence and side effects of gadget addiction but it lacking in proven and published cost-effective, promising, and convenient Ayurveda therapy for gadget-addicted children. Are search gap exists with special reference to the use of Ayurvedic interventions for the management of gadget addiction in children.

The Ayurveda concepts of Asatmeindriyartha Samyoga [9] (inadequate association of senses with their organs of perception) and Pradnyaparadh (misuse of intellect) go much further to today’s gadget addiction. Rather, it helps stimulate gadget addiction. The word Pradnyaparadha [10] is a combination of 2 words, that are Pradnya and Aparadh. Pradnya encompasses Dhee (intellect), Dhruti (control), and Smriti (memory), and Aparadh means misdemeanor. In addiction (could be of any type), the mental ability of the affected person is compromised, affecting their decision-making power. The mind needs controlling power to make decisions. According to Ayurveda, Dhee is the factor that governs the action of the mind [11]. Satva, Raja, and Tama Manas Guna also play an important role in the decision-making power and emotions of a person. Many features of gadget addiction are similar to the clinical features of Raja and Tama Guna’s predominance [12]. Hence, to achieve a normal mental equilibrium in a person, we need to increase satva guna and decrease Tama and Raja Guna. This can be achieved by adequate counseling, assurance, Sadvritta Palana (Ayurveda rules to prevent mental and physical disorders), Dhyana (meditation), and the use of the Medhya Rasayana [13]. Medhya Rasayana means the drugs that promote Medha, which has Dhee (intellect), Dhruti (control on mind), and Smriti (memory) as its components [14]. Medhya Rasayana enhances the Sadhaka pitta, which is responsible for Nischayatmaka Buddhi [15] that is the decision-making power to opt for the right thing over wrong.

Gadget addiction is a behavioral disorder. There is research evidence of the use of antidepressants and antianxiolytic drugs for the management of gadget addiction [16]. The antidepressant and anxiolytic effects of Medhya drugs have proven efficacy, as reflected in various previous studies [17]. Medhya Rasayana acts on the hypothalamus-pituitary-adrenal axis and normalizes the secretion of serotonin and acetylcholine, thereby improving mental function [18]. The classical texts of Ayurveda describe Satvavajaya Chikitsa (subjugation of mind) for the management and prevention of behavioral, psychogenic, and lifestyle-related disorders [19]. Satvavajaya (subjugation of mind) helps a person to control the mind and restrain it from unwholesome objects by playing a significant role in maintaining a harmonious state between intellect, memory, and patience, leading to a healthy mental condition. Practical approaches of Satvavajaya Chikitsa are Ashwasana (reassurance and explanation), Pratidwanda Chikitsa (replacement of emotions), Chintya (presumption), Dhyeya (correction of objectives and ideas), Sankalpa (proper guidance and advice for taking the right decision), Dhriti (proper control of patience), Suhritvakya (guidance and suggestion), Dharmarthavakya (education of individual and family), Santwana (rehabilitation and assurance) [20]. Applying the above methods could change children’s thinking and restrain them from unwholesome things. It could be beneficial in the management of Gadget addiction. Changing the thinking power of a patient is very important in the case of any addiction; this will happen with the help of Satvavajaya Chikitsa. Sadvritta helps in maintaining physical and mental fitness [21]. This helps improve the quality and longevity of life by secreting happy hormones [22]. It supports an increase in the Satvik guna of mind. Nonpharmacological measures like Sattwavajaya Chikitsa (subjugation of mind) dealing with manonigraha (control over unwanted thoughts and desires of mind) and proper counseling of patients, along with improvising the patient’s self-confidence. Along with this, yogic (postures and meditation) therapy and lifestyle modifications are very beneficial to keep the body and mind healthy and calm. Yoga enables the person to restrain from addiction by promoting self-regulation. Yoga has the potential to detoxify our mind and body and it is also capable of controlling emotions. This phenomenon is useful in addiction craving, compulsive behavior, tolerance, and relapse conditions [23]. Yoga induces dopamine homeostasis, leading to long-term benefits for various addictive behaviors [24].

### Protocol

#### Study Objectives

Evaluation of comparative efficacy of Medhya Rasayana (pharmacological) intervention versus Ayurveda nonpharmacological interventions and cognitive behavioral therapy in gadget addiction in children of the age group of 6 to 16 years.

The objectives of this study are listed in Textbox 1.

Primary and secondary objective.
**Primary objectives**
To evaluate the efficacy of Medhya Rasayana in gadget addiction with an internet addiction test scale, a digital addiction scale, and *DSM-5* (*Diagnostic and Statistical Manual of Mental Disorders* [Fifth Edition]).To evaluate the efficacy of Ayurveda nonpharmacological interventions in gadget addiction with an Internet addiction test scale, a digital addiction scale, and *DSM-5*.To assess the comparative efficacy of 3 therapeutic modalities in the management of gadget addiction by Internet addiction test scale and *DSM-5*.

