
**Figure 1 figure1:**
[figure not shown]
Consolidated Standards of Reporting Trials (CONSORT) flow diagram.

Inclusion and exclusion criteria.Inclusion criteriaParticipants irrespective of gender, religion, and socioeconomic status.Participants affected with gadget addiction as per case definition, that is internet addiction test score: 31-79.Age group between 6-16 years with signs and symptoms of gadget addictions as per *ICD-10* (*International Statistical Classification of Diseases, Tenth Revision*) or 11 as follows.Parents who are willing to provide written informed consent for their children to be included in the study.Exclusion criteriaInternet addiction test score >80.Children aged <6 years and those aged >16 years.Parents who are not willing to provide written informed consent for their children to be included in the study.Children experiencing from behavioral diseases, locomotor diseases, genetic diseases, and systemic disorders.

**Table 1 table1:** Overview of interventions.

	Group P	Group N	Group C
Participants, n	80	80	External group
Name of medication	Medhya Rasayana	Nonpharmacological	Cognitive behavioral therapy
Dosage form	Young’s formula	As per schedule	—^a^
Duration	90 days	90 days	—
Assessment with IAT^b^ scale	0, 30, 60, and 90 days	0, 30, 60, and 90 days	—
Follow up with the IAT scale, digital addiction scale, and *DSM-5*^c^ scale	180th day	180th day	—
Route or mode of administration	Oral	—	—
Anupana	Lukewarm water	—	—

^a^Not applicable.

^b^IAT: internet addiction test.

^c^*DSM-5*: *Diagnostic and Statistical Manual of Mental Disorders* (Fifth Edition).

**Table 2 table2:** Overview of Ayurveda nonpharmacological intervention.

Intervention	Details of method	Duration and frequency
Counseling (Satvavajaya)	Counseling about hazardous effects of mobile and benefits of mobile deaddiction	Fortnight 1 session with parents and child separately
Yoga therapy	Surya Namaskar, Dhyana	Daily
Encouragement for indoor and outdoor games	Patients will be counseled to play indoor and outdoor games daily	Daily for1hour
Encouragement towards attending social programs	Parents will be guided for engagement of children in learning new things, in group activities with peers, etiquette	“Si-opus sit” Whenever required and feasible
Encouragement of parent-child relationship	Parents are advised to spend time with their children. And advised to give a reward for not using mobile to child.	Minimum 2 hours of quality time daily by parents

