### Participants

The required sample size was calculated by using the following formula.

To evaluate the effectiveness of the therapeutic modalities for managing internet addiction, several key parameters are defined. The type I error rate () is set at 5% and the type II error rate (β) is set at 20%. The true proportion difference, represented by ε, is assumed to be 0. δ denotes the clinically relevant difference at 20% superiority. Initially, the proportion of individuals with internet addiction (P1) is 62.22% (0.622). After the intervention (P2), this proportion decreased to 36.2% (0.362). To determine the appropriate sample size for the study, a clinically accepted difference of 20% is used. The sample size is calculated according to the formula N=(1.64+0.84)2(0.622)(1–0.622) +0.362(1–0.362)/(0.20)2. Based on this formula, the required sample size is 72 individuals per group. To account for a 10% dropout rate, the sample size is increased to 80 per group.

Therefore, 80 participants will be recruited after randomization in each group from the Kaumarbhritya OPD of Mahatma Gandhi Ayurved College Hospital and specialty camps held in peripheral villages of Wardha city. A computer-generated random number table will be used to avoid selection bias in the study. The principal investigator will carry out the process of randomization and enroll the participants. To be eligible for participation, participants should fulfill the inclusion criteria as mentioned in Textbox 2. Patients having any characteristics of exclusion criteria will be excluded from participation in the study.

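### Primary objectives 1 and 2 claim stand-alone efficacy for each arm, but without a concurrent untreated group a within-arm fall cannot be separated from regression to the mean, natural course or expectation

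*Protocol article*

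**What the plan says.** Textbox 1 of the protocol article lists three primary objectives. Two take one arm at a time: "To evaluate the efficacy of Medhya Rasayana in gadget addiction with an internet addiction test scale" and "To evaluate the efficacy of Ayurveda nonpharmacological interventions in gadget addiction with an Internet addiction test scale", each with further scales. Comparison is kept for the third: "To assess the comparative efficacy of 3 therapeutic modalities in the management of gadget addiction".

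Under Study Design, children are randomised 1:1 between the two Ayurveda arms only. The third arm is not enrolled: "Group III will be the external group due to the fact that cognitive behavioral therapy requires trained professionals", and its results come from "published data of previously conducted clinical trials".

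Entry (Textbox 2) is by score on the outcome scale: "Participants affected with gadget addiction as per case definition, that is internet addiction test score: 31-79". Scores above 80 are excluded. The IAT is repeated on days 0, 30, 60, 90 and 180, and child and parent ratings are averaged (Assessment of Participants). Study Design also provides for removing children who do not respond or do not follow instructions.

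The sample-size text under Participants takes 62.2% as the initial proportion with internet addiction and continues: "After the intervention (P2), this proportion decreased to 36.2% (0.362".

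**The concern.** An efficacy objective needs a contrast that shows what would have happened without the treatment. Objectives 1 and 2 name none, and the design provides none. P versus N shows only whether one active treatment does better than the other. The published data are neither concurrent nor untreated. What is left is each arm's change from day 0.

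That change has several sources besides treatment:

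- Children are selected on a score that is then remeasured.
- They come because a parent wants the gadget use treated, and the problem may ease with time.
- Child and parent supply the ratings, and both know whether the child takes an oral preparation or follows a yoga and counseling programme.
- If the removal rule in Study Design covers children whose scores do not improve, dropping them raises the average improvement of those who remain.

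At stake are two of the three primary claims. The Conclusion section expects the results to guide treatment and inform policy makers, so a within-arm fall read as efficacy would have consequences.

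**Working it through.** **1. Is change from baseline really the evidence?** Textbox 1 does not say so. Three possible comparators can be checked against objectives 1 and 2:

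| Possible comparator | What it can show |
|---|---|
| The other randomised arm | Relative efficacy only; already objective 3 |
| Published cognitive behavioral therapy data | Non-randomised contrast with an active treatment |
| The arm's own baseline | Change, whatever its cause |

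Only the last uses one arm alone, as the objectives do. The sample-size text points the same way, because its two proportions are before and after intervention.

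**2. The plan's own figure.** n = (1.64 + 0.84)² × [0.622 × 0.378 + 0.362 × 0.638] / 0.20² = 6.1504 × 0.466072 / 0.04 = 71.66, so 72 per group. Allowing for 10% dropout, 72 / 0.90 = 80. Both stated figures reproduce and neither is disputed. The before-after fall in the text is 0.622 − 0.362 = 0.260.

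**3. Size of regression to the mean with no treatment effect.** The article gives no IAT mean μ, SD σ or retest correlation ρ for the children screened, so all three are assumptions. For bivariate normal scores with entry at 31 to 79:

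expected fall = (1 − ρ) × (mean baseline of those selected − μ).

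- Largest fall in the main grid: μ = 30, σ = 17, ρ = 0.6. The selected mean is 44.04, so the fall is 0.4 × 14.04 = 5.6 points.
- Smallest: μ = 40, σ = 15, ρ = 0.8. The selected mean is 46.65, so the fall is 0.2 × 6.65 = 1.3 points.
- Centre of the window: (31 + 79) / 2 = 55. Selection is then symmetric, the selected mean is 55, and the fall is 0.

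**4. How often a within-arm test would be significant.** Paired t test, two-sided 5%, n = 72, critical value 1.994. SDs of the differences are from simulation.

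- μ = 30, σ = 15, ρ = 0.6: fall 5.03, SD of differences 12.50, standard error 12.50 / √72 = 1.473, ratio 3.41. The chance of a significant fall is about Φ(3.41 − 1.99) = 92%.
- μ = 40, σ = 15, ρ = 0.8: fall 1.33, SD of differences 9.24, standard error 1.089, ratio 1.22. The chance is about Φ(1.22 − 1.99) = 22%.

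| Source mean (SD 15 to 17, ρ 0.6 to 0.8) | Mean fall, IAT points | Significant fall in one arm |
|---|---|---|
| 30 to 40 | 1.3 to 5.6 | 22% to 92% |
| 45 | 0.8 to 2.0 | 12% to 22% |
| 55 | about 0 | about 2.5% |

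For independent arms, both would be significant with probability 0.22² to 0.92², about 5% to 85%, over the first row.

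**5. On the proportion scale.** In the first row, 12% to 31% of selected children score below 31 at retest with no effect. The plan's 20% difference and 26-point fall are proportions, so this is the quantity to set beside them, not the IAT points. The comparison is only rough: all the simulated children start at 31 or above, whereas the plan's initial proportion is 62.2%.

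**The case against.** The strongest reply is that the trial is comparative. The overall aim concerns comparative efficacy, the design is called a superiority trial, and the alternative hypothesis says the Ayurveda interventions "are more effective than the control group in reducing gadget addiction in children". No within-arm test is named under Statistical Analysis. This stands in part: the before-after reading is an inference. It does not rescue objectives 1 and 2, because that control group is the external data and cannot show whether either arm does better than no treatment.

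Second, the simulated source means are chosen. Children must also have signs and symptoms under ICD-10 or 11, and some come from an outpatient department, so the true mean may be higher. Village camps are a source too, so it is unknown. Averaging two raters may raise reliability: at a correlation of 0.9 with source mean 30 to 40, the fall is only 0.7 to 1.4 points. Excluding high scorers offsets part of the fall. All of this stands, and it limits what can be said about size.

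Third, the Discussion lists the lack of a proven Ayurvedic control group as a limitation. That is partial disclosure, but the objectives are unchanged.

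A reader might infer that both arms will almost surely appear effective, or that the protocol announces a before-after test. The documents support neither. On the main grid the chance that both arms are significant runs from about 5% to 85%, and near a source mean of 55 there is no inflation.

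**Conclusion.** The concern holds as a matter of design. The plan sets two primary efficacy claims that its arms cannot support, and no later analysis plan can supply the missing concurrent control. A within-arm fall cannot be distinguished from regression to the mean, natural course or expectation.

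The share due to regression to the mean is conditional on figures the article does not give. It could be large enough to produce a significant fall in most trials, or close to zero. The other sources remain even where it is zero. Two links rest on reading rather than explicit text: that objectives 1 and 2 will be judged by change from baseline, and that the removal rule covers children who do not improve.

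**What to change.** Reword objectives 1 and 2 as: to describe the within-arm change in P and in N, with 95% intervals. State that no efficacy conclusion will be drawn from within-arm tests. Rest the randomised conclusion, which is one of relative efficacy, on the P minus N difference in IAT at day 90. Keep the cognitive behavioral therapy comparison in objective 3 as a separate comparison, labelled non-randomised; nothing here argues for dropping it.

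The change is to wording only and needs no extra children or visits. The cost is that the sponsor gives up two claims the design cannot support.
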